## Abstract

**Background**: Frailty is highly prevalent among older adults with cardiovascular disease (CVD) and strongly predicts disability and mortality after cardiac events. Although cardiac rehabilitation (CR) improves prognosis, frail older patients often face barriers to participating in in-person programs. eHealth-based, home-delivered CR programs incorporating tele-rehabilitation and remote monitoring may improve accessibility, yet evidence regarding their effectiveness on frailty status remains limited. **Methods**: We designed a multicenter, randomized, parallel-group trial enrolling people ≥65 years recently hospitalized for acute heart failure (AHF) and/or acute coronary syndrome (ACS). Participants were randomized 1:1 to an eHealth home-based tele-rehabilitation program or the usual care. The primary endpoint is frailty prevalence at follow-up, defined by an Essential Frailty Toolset (EFT) score ≥3, with co-primary outcomes being between-group differences in the mean levels of EFT and Short Physical Performance Battery (SPPB) scores after 3–6 months. Secondary endpoints include mortality and hospitalization, among others. **Results**: The full protocol and study procedures are reported. Between May 2024 and December 2025, 589 patients were screened at the two Italian centers involved; 442 met eligibility criteria and 209 were enrolled and randomized. Baseline characteristics were largely comparable between groups. The mean age was 77 ± 9 years, 70% were male, and 55% had ACS. Lower-than-expected enrollment was mainly attributable to refusal related to difficulties in using digital devices. **Conclusions**: This randomized trial will evaluate whether a multidomain, eHealth-based CR intervention can reduce the prevalence or degree of frailty in older people after AHF or ACS. We report the study protocol and baseline characteristics of the enrolled cohort, highlighting the challenge of digital illiteracy in contemporary older populations.

## 1. Introduction

Older people with cardiovascular disease (CVD) are particularly vulnerable, exhibiting both high mortality [1] and a consistent risk of disability following hospitalization [2]. A major determinant of such poor outcomes is frailty, a clinical syndrome highly prevalent among older individuals with CVD [3]. Frailty is characterized by a progressive decline in the physiological reserves of multiple organ systems, which limits the individual’s ability to cope with stressors and predisposes them to negative health trajectories. As an independent predictor of autonomy loss, frailty is strongly associated with adverse clinical outcomes, including hospital readmissions, institutionalization, and death [4].

Preliminary evidence suggests that frailty may not represent an irreversible condition, raising the possibility that targeted interventions could improve resilience and potentially alter the course of the syndrome [3]. Cardiac rehabilitation (CR) programs are established as effective tools to improve cardiovascular prognosis and quality of life [5]. However, despite their proven efficacy, the uptake of CR remains suboptimal, with older and frail patients facing the greatest barriers due to mobility limitations, comorbidities, and thus a limited access to structured programs. In this respect, digital health interventions offer the opportunity to extend the reach and adaptability of traditional models. By facilitating adherence, enhancing accessibility, and supporting individualized care, eHealth-based CR programs, which incorporate tele-rehabilitation (TR) and remote monitoring, have the potential to overcome many of the barriers encountered by older patients [6]. However, few studies have explored the efficacy of eHealth home-based CR interventions on frailty. Indeed, a recent systematic review concluded that more studies are needed to define its efficacy and usefulness to make definitive recommendations [7].

To fill this gap, we undertook a randomized trial to evaluate whether an eHealth home-based CR intervention, compared with the standard of care, is able to reduce the rate or the degree of frailty in people ≥ 65 years and with acute heart failure (AHF) and/or acute coronary syndrome (ACS). Here we report the protocol of the trial and the baseline clinical data of included participants.

## 2. Materials and Methods

### 2.1. Study Design

This is a multicenter, randomized, parallel-group study in older patients with a recent hospitalization for AHF and/or ACS, conducted at two study sites: IRCCS MultiMedica, Sesto San Giovanni (MI), Italy, and Istituti Clinici Scientifici Maugeri IRCCS, Cardiac Rehabilitation Unit of Bari Institute, Bari, Italy. People with AHF or ACS and ≥ 65 years old were randomized into two groups: Group (A), a multidisciplinary eHealth home-based TR program; and Group (B), which received the usual care. After a minimum of 3 and up to a maximum of 6 months, enrolled subjects underwent a new evaluation for frailty. The duration of follow-up was flexible to facilitate participation and adherence. The latest available follow-up will be considered for each individual and mixed models will be used to account for different times to follow-up in the analyses. A summary of study design is presented in Figure 1. Given the nature of the study involving an active intervention only in the group assigned the eHealth arm, the trial was not blinded, i.e., investigators performing the frailty screening both at baseline and follow-up were also involved in the development of the program. The help of a caregiver was allowed but was not mandatory to participate to the study. Caregivers were not in charge of exercise supervision.

### 2.2. Study Endpoints

#### 2.2.1. Primary Endpoints

The primary endpoint is to assess whether a home-based TR program significantly reduces the prevalence of frailty in comparison to usual care in older individuals hospitalized for ACS and/or AHF. Frailty status is defined as having an Essential Frailty Toolset (EFT) score (ranging from 0 to 5) ≥ 3 [8].

Since the recent literature suggests that frailty is a progressive continuum and not a present/absent condition [9,10] and considering that small improvements in the degree of frailty are associated with tangible benefits [11], the mean degree of frailty was considered as a co-primary endpoint. In particular, mean differences between groups at the end of treatment in the EFT and Short Physical Performance Battery (SPPB) scales were set as co-primary outcomes after the start of the enrollment due to the considerations reported above. After termination of the enrollment, we observed that the study is powered to detect a difference in these co-primary outcomes, while the power for the primary outcome of frailty prevalence is lower than initially planned. Thus, this and the other secondary endpoints will be considered as exploratory.

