### 2.22. Data Collection and Statistical Analysis

Study data were collected in the eCRF of an electronic web-based database, where each patient is identified by a randomly assigned alphanumeric code that is center-specific.

Baseline data were analyzed through descriptive analyses. Results for the overall population and for both Groups A and B are presented. Categorical variables were presented as frequencies and percentages and compared between the two groups by Chi-square test of Fisher’s exact test. Continuous variables were summarized by mean ± standard deviation and tested for normality distribution by Kolmogorov–Smirnov test. Since all variables were not normally distributed, the non-parametric Wilcoxon–Mann–Whitney U test will be used to compare baseline variables between groups. The prevalence of frail patients in the two groups is indicated as an EFT score ≥ 3. For the planned analyses, mixed models, adjusted for unbalanced variables, will be used to account for different times to follow-up. Only people with available measures of EFT at both baseline and follow-up will be included in the analyses relative to the prevalence of frailty and EFT as a continuous variable, while only individuals with available measures of SPPB at both baseline and follow-up will be included in the analyses for this endpoint. For the other covariates, missing data will be imputed through regression models. Given the limited sample size, subgroup analyses are not planned.

All analyses were performed by using SAS Software version 9.4. Tests will be considered significant for a *p* value < 0.05.

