## 4. Discussion

The efficacy of eHealth-based, home-delivered CR interventions on frailty is debated [7]. To address this gap, we designed a randomized trial evaluating whether an eHealth CR program, compared with standard care, can reduce the prevalence or degree of frailty in patients >65 years hospitalized for AHF or ACS. Here we outline the trial protocol and report the baseline characteristics of the enrolled participants.

The number of enrolled individuals is lower than the planned sample size for the primary outcome, but sufficient for the co-primary outcomes. Thus, the study will be powered to detect a difference in the mean level of frailty but not to observe a difference in the prevalence of frailty considered as a binary variable, unless a higher-than-expected efficacy of the intervention emerges. Indeed, the study now reaches a power of 55% for the primary outcome when considering an expected difference of 13% in the final prevalence of frailty, while a difference of 17% in the prevalence of frailty would be needed to obtain a significant result. This aspect is of relevance, especially in case of non-significant findings.

The lower-than-expected enrollment capacity is attributable to the high rate of refusal to participate due to the reported inability or fear of using technological devices such as a tablet. These phenomena commonly, referred to as “digital illiteracy” and “technophobia”, are common in the oldest old and particularly pervasive in Italy [24]. As a result, we had to amend the protocol after the start of the study to lower the cutoff for age of inclusion in the study. We believe that this does not represent an issue since, as discussed, frailty represents a continuum with a broad spectrum of conditions that should be addressed as early as possible and not only when severe comorbidities are present [9,10]. In this respect, this consideration also emphasizes the relevance of the results, which will demonstrate whether an eHealth-based, multidomain intervention is able to affect the degree of frailty when considered as a continuous, and not binary, variable.

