Relative to the composition of the groups, these are well balanced, as expected by the randomization process. The only variables not balanced are sex and the SPPB. Thus, the analyses will be adjusted for such covariates, given their known relationship with the primary outcomes [25]. Cox models and ANCOVA, both adjusted for these unbalanced variables, were used to compare the prevalence and the degree of frailty, respectively. A sensitivity analysis using propensity score matching was also performed. In the active arm of the trial, 45 people performed low-level-intensity exercises and the others underwent a high-level program. Given this limited sample, subgroup analyses are not adequately powered and cannot explore whether the intervention is more effective in people with a low SPPB score, despite the prior literature suggesting that the frailest individuals (i.e., SPPB < 10) would show greater improvement [26].

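### Frailty prevalence is labelled both primary and exploratory, and the two co-primary scales are each tested at 0.05 with no rule on whether one or both must succeed

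*Protocol article*

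**What the plan says.** On the status of frailty prevalence:

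- Abstract: "The primary endpoint is frailty prevalence at follow-up, defined by an Essential Frailty Toolset (EFT) score ≥3". The abstract does not mention any demotion.
- Section 2.2.1 opens by naming prevalence as the primary endpoint and closes with "Thus, this and the other secondary endpoints will be considered as exploratory".
- Section 4 (Discussion) keeps the old label: "the study now reaches a power of 55% for the primary outcome when considering an expected difference of 13" percentage points. It also discusses how large a difference would be needed for significance.

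On the co-primaries and the timing of the changes (section 2.2.1):

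- The mean differences on the EFT and SPPB "scales were set as co-primary outcomes after the start of the enrollment due to the considerations reported above".
- The demotion of prevalence came later and rests on power: "After termination of the enrollment, we observed that the study is powered to detect a difference in these co-primary outcomes".

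On the decision rule:

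- Section 2.22: "Tests will be considered significant for a" p value below 0.05. The article gives no alpha split, testing order or either/both rule.
- Section 2.20 sizes prevalence and mean EFT separately, each at the full 5% alpha. For SPPB it says only that the result was similar.
- The abstract states the aim as whether the intervention can "reduce the prevalence or degree of frailty in older people after AHF or ACS". The Introduction and the Discussion use the same either/or form.

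**The concern.** There are two linked defects. First, the article gives one endpoint two incompatible roles, so a reader of the abstract and a reader of section 2.2.1 would judge the trial on different endpoints. Second, once prevalence is set aside, two confirmatory endpoints remain, each with its own 0.05 test and no statement of what counts as success. The either/or wording of the aim makes it easy to claim a positive trial on whichever scale is significant.

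The context makes a fixed rule more important. The co-primaries were introduced during enrolment, and prevalence was demoted after enrolment ended because its power was low. Section 2.1 says the trial is unblinded and that the investigators assessing frailty also helped develop the programme. A success rule chosen after the results are known would not be credible, and a positive result on one scale alone would look like endpoint switching even if it were not.

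**Working it through.** **1. The plan's own figures, to see what alpha they use.**

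*Prevalence (section 2.20: 21% v 34%, 80% power, alpha 5%).* With a pooled proportion of 0.275:

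n per arm = [1.96·√(2·0.275·0.725) + 0.842·√(0.21·0.79 + 0.34·0.66)]² / 0.13² = 184.0, rounded up to 185, so 370 in total. This matches the stated 370.

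*Power for prevalence with 103 per arm.* The same formula solved for power gives 55.2%, against 55% in the Discussion.

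*Mean EFT (section 2.20: 1.25 v 1.95, SD 1.25, 90% power, alpha 5%).*

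n per arm = 2·(1.960 + 1.282)²·(1.25/0.70)² = 67.0, rounded up to 68, so 136 in total. This matches the stated 136.

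All three reproduce at an unadjusted two-sided 0.05. No alpha was reserved for a second endpoint.

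**2. Error if either co-primary is enough.** For two independent tests at 0.05:

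1 − 0.95² = 9.75%.

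For two-sided normal tests, independence is the worst case, so 9.75% is an upper limit. The EFT and SPPB both include a chair-rise task (section 2.6), so some correlation is likely. The article gives no value, so a range is shown (2 million simulated pairs of null z statistics per row, critical value 1.96):

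| Assumed correlation | Either significant | Both significant |
|---|---|---|
| 0 | 9.8% | 0.2% |
| 0.3 | 9.5% | 0.5% |
| 0.5 | 9.1% | 0.9% |
| 0.7 | 8.3% | 1.6% |
| 0.9 | 7.0% | 3.0% |

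**3. Error if both are required.** A false claim needs the test of at least one truly null endpoint to be significant at 0.05. The error is therefore at most 5%, whatever the correlation and even if the other endpoint has a real effect.

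**4. What control would cost for EFT.** Using the plan's difference of 0.70 and SD of 1.25, power = Φ(0.56·√(n/2) − z), where 0.70/1.25 = 0.56. Evaluable n per arm is taken as 103 (no loss) or 80 (103 × 0.78, the plan's 22% dropout).

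| Two-sided alpha | z | n = 80 per arm | n = 103 per arm |
|---|---|---|---|
| 0.05 | 1.960 | Φ(1.58) = 94.3% | Φ(2.06) = 98.0% |
| 0.025 | 2.241 | Φ(1.30) = 90.3% | Φ(1.78) = 96.2% |

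The same sum cannot be done for SPPB, because section 2.20 gives no SPPB difference or SD. Table 2 shows baseline SPPB for 171 of 206 patients, and section 2.22 limits that analysis to patients with both measurements.

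**The case against.** The strongest reply is that section 2.2.1, read in time order, already settles the hierarchy: prevalence came first, the two scales were added, and prevalence was then made exploratory with the reason disclosed. The labels left in the abstract and Discussion would then be a drafting slip. This is fair, and it means there are two confirmatory endpoints. A reader might otherwise count three chances and reach 1 − 0.95³ = 14.3%. The article does not support that: it makes prevalence exploratory, and EFT of 3 or more is a cut of the same score as mean EFT, so the tests cannot be independent.

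Second, co-primary is often taken to mean that both must succeed, and the either/or wording contrasts binary with continuous frailty rather than setting an EFT-or-SPPB rule. This also stands in part. Inflation follows from one reading only. But the article never adopts the other reading, and its wording of the aim does not point there.

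Third, this is a condensed article; a deposited protocol is cited in section 2.25 and an analysis plan may exist. Details such as the dates of amendments may be there. That does not cure the contradictory labels, or a p-value criterion applied to two co-primaries without a rule, both of which are fixed in this text.

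Fourth, the Discussion says that adjusted models "were used to compare the prevalence and the degree of frailty, respectively", and a reader might infer that outcomes had been seen before the hierarchy was set. The article does not show this. Its tenses are mixed throughout, the abstract speaks of the evaluation as still to come, and the stated reason for the demotion is power.

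**Conclusion.** The concern holds in this form: the status of frailty prevalence is contradictory within the article, and the success rule for the two co-primaries is unstated. If a claim may rest on either scale, the familywise error is at most 9.75%, and about 7.0% to 9.5% for assumed correlations of 0.9 to 0.3. If both must succeed, it is at most 5%. The size of the problem therefore depends on a rule that the article does not give.

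A reader might also infer that joint power for the two scales falls short of the stated 90%. That cannot be concluded. The 90% is stated for EFT alone, EFT power on the planning inputs is about 94% at 80 per arm, and there are no SPPB inputs from which to compute a joint figure.

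The matter should be settled before outcomes are analysed by arm, because it decides what the trial may claim. The EFT power figures rest on the plan's assumed difference and SD, not on trial data.

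**What to change.** 1. Use one hierarchy in the abstract, section 2.2.1, section 2.22 and the Discussion. Describe frailty prevalence as the original primary endpoint, now exploratory, and report it by estimate and 95% CI with no confirmatory claim. Reword the either/or aim to match.
2. Before outcomes are analysed by arm, fix one error-controlling rule for mean EFT and mean SPPB. Any of these would do:
   - a fixed sequence, with EFT first at two-sided 0.05 and SPPB at 0.05 only if EFT is significant; EFT power is unaffected, but SPPB cannot be claimed if EFT fails;
   - both required at 0.05; neither scale can then carry a claim alone;
   - 0.025 for each scale; EFT power is about 90% at 80 per arm and 96% at 103 per arm.
3. State whether each endpoint change (adding the co-primaries, demoting prevalence) was made without sight of outcome data by arm.

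The cost is wording only, with no extra patients and little or no loss of EFT power. The effect on SPPB power cannot be given until its planning inputs are reported.

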#### 2.2.2. Secondary Endpoints

A composite endpoint of all-cause death and all-cause hospitalizations.A composite endpoint of cardiovascular death and cardiovascular hospitalizations (ACS, AHF, cardiac arrhythmias, cerebrovascular events, peripheral arterial vascular event).Changes in walking distance during 6 min walk test at follow-up vs. baseline in the two groups.Assessment of the quality of life, comorbidity burden, nutritional and cognitive status, depression, adherence to medical therapy and anthropometric measures. Tools for the evaluation of these endpoints are described below.Incidence of falls during follow-up.Proteomic and miRNOmic analyses to search for biomarkers of frailty.

### 2.3. End of Study Definition

The end of the study is defined as the date of the last visit for the last subject in the study. A participant is considered to have completed the study if they have completed all steps of the protocol.

### 2.4. Study Population

#### 2.4.1. Inclusion Criteria

Age ≥ 65 yrs. The protocol was modified after the start of the study to lower the previous threshold of 75 years due to the high rate of refusals to participate attributable to the self-reported inability of older individuals to use technological devices (as detailed below).Recent (<30 days) hospitalization for AHF or ACS.Signed informed consent.

#### 2.4.2. Exclusion Criteria

Judgment by the investigator that the participant is unlikely to comply with study procedures (i.e., ability of patient or caregiver in utilizing eHealth device).Other medical conditions determining a ≤6-month survival prognosis.Severe cognitive impairment, assessed through Mini Mental State Examination (MMSE < 15).Participation in another clinical study with a study intervention administered in the last 4 weeks.

### 2.5. Study Procedures

Step 1. Patients were screened and recruited during hospitalization in the Cardiovascular Department of IRCCS MultiMedica (Sesto San Giovanni—MI, Italy) or Cardiac Rehabilitation Unit of IRCCS ICS Maugeri (Bari—BA, Italy). The main clinical and demographic data were collected for each patient. The day before discharge, patients performed a 6 min walk test, gave a blood sample to test for molecular biomarkers and underwent a frailty evaluation on both the EFT and SPPB scales. Depression, quality of life, cognitive status, nutritional status, and adherence to medical therapy were evaluated with adequate tools. Blood samples were collected to identify biomarkers able to identify frailty and predict its progression.

Step 2. Before discharge, all enrolled patients were randomized in a 1:1 ratio to intervention (Group A) or usual care (Group B). Group A followed a multidisciplinary home-based TR program while Group B was referred to general practitioners (GPs).

Step 3. The home-based TR program was implemented in Group A patients. Group B was referred to GPs according to usual care. During step 3, clinical outcomes and adverse events were collected.

Step 4. After at least 3 and at most 6 months of follow-up, patients underwent final evaluation; the procedures of step 1 were repeated. Study procedures are summarized in Supplementary Table S1.

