### 2.21. Randomization

Patients were randomly assigned in a 1:1 ratio to the intervention or control group through permuted-block randomization with varying block sizes. Randomization lists were center-specific and they were created using SAS^®^ Proc Plan permuted-block randomization. A list was created for each center. The lists were created with block sizes of 2, 4, and 6. The order of block permutations was then randomized within each list to avoid predictability. A seed was set for generating the list so that it could be reproduced if necessary. Patient allocation was performed via a centralized email system.

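### The two centres recruit from different kinds of unit, yet centre, the randomisation stratum, is missing from the stated adjustment set and no result by centre is planned

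*Protocol article*

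**What the plan says.** The aim in section 1 (Introduction) is "to evaluate whether an eHealth home-based CR intervention, compared with the standard of care, is able to reduce the rate or the degree of frailty". Section 2.5 (Study Procedures) describes recruitment at the first centre as follows: "Patients were screened and recruited during hospitalization in the Cardiovascular Department of IRCCS MultiMedica". The second recruiting unit is the "Cardiac Rehabilitation Unit of IRCCS ICS Maugeri (Bari—BA, Italy". Section 2.1 and the Figure 1 legend also name the Bari unit in this way.

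Baseline is tied to the end of the stay: "The day before discharge, patients performed a 6 min walk test", and EFT and SPPB were assessed at the same point. Eligibility in section 2.4.1 is "Recent (<30 days) hospitalization for AHF or ACS". After allocation, care is described identically for both centres: "Group A followed a multidisciplinary home-based TR program while Group B was referred to general practitioners (GPs".

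On allocation, section 2.21 states "Randomization lists were center-specific", at 1:1. On analysis, section 2.22 adjusts for unbalanced variables, and section 4 (Discussion) identifies these as sex and SPPB. Centre is not named. Section 2.22 adds: "Given the limited sample size, subgroup analyses are not planned". Tables 1 and 2 give nothing by centre, and the only heterogeneity discussed is heart failure against coronary syndrome.

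**The concern.** Discharge from a cardiovascular department and discharge from a cardiac rehabilitation unit are not obviously the same starting point. If the stay in Bari included rehabilitation, the trial there compares continued rehabilitation at home with GP referral after inpatient rehabilitation. At the other centre, home tele-rehabilitation may be the first rehabilitation offered. Room for improvement and the size of the effect could differ between the two, and a single label of usual care does not tell the reader which situation the pooled estimate describes.

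This bears on the trial's rationale, which rests on older and frail patients facing the greatest barriers to structured programmes. Patients recruited inside a rehabilitation unit have at least reached such a service.

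There is also a plain analysis point. Centre is the stratification factor and here also marks the recruiting setting. A rule that selects covariates because they are unbalanced will tend to pass over centre, since blocked lists within centre keep it balanced by design. If centre predicts the outcome, leaving it out costs precision.

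**Working it through.** **Inputs.** From section 2.20: end-of-study EFT means of 1.25 (intervention) and 1.95 (control), hence a difference of 0.70; SD 1.25; two-sided alpha 5% (sidedness assumed); power 90%; dropout 22%. From section 3 and Table 1: 103 + 103 = 206 patients. The split by centre is not given, so I use 30%, 50% and 70% as an assumed range.

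**The plan's own figure.** n per arm = 2(1.96 + 1.2816)² × 1.25² / 0.70² = 67.01, rounded up to 68, so 136 in total. This matches section 2.20, so the point does not rest on an arithmetic error.

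**Patients analysed.** 206 × 0.78 = 160.7, about 161, or 80.5 per arm. Pooled standard error = 1.25 × √(2/80.5) = 0.197, giving a 95% half-width of 0.39 and power of about 94% for a difference of 0.70.

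**Precision within one centre.** Half-width = 1.96 × 1.25 × √(2/n), with n per arm in that centre.

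| Share of patients in that centre | n per arm | Half-width (EFT points) | Power for 0.70 |
|---|---|---|---|
| 30% | 24.1 | 0.71 | 49% |
| 50% | 40.2 | 0.55 | 71% |
| 70% | 56.3 | 0.46 | 84% |

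**What an interaction test could show.** The standard error of the difference between the two centre effects is √(SE₁² + SE₂²).

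- At 50:50, each centre's SE is 0.279, so the interaction SE is 0.279 × √2 = 0.394. Suppose the effect is 0.70 at one centre and 0.35 at the other, a difference of 0.35. Then 0.35/0.394 = 0.89, and power is Φ(0.89 − 1.96) plus a negligible far tail, about 14%.
- At 30:70, the interaction SE is 0.43 and power is about 13%.
- For 80% power the two effects would have to differ by (1.96 + 0.84) × 0.394 = 1.1 points at 50:50, or 1.2 at 30:70. Both exceed the whole planned effect of 0.70.

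So per-centre estimates can describe the data, but a test cannot establish whether the effects agree or differ.

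**The case against.** The strongest objection is that the premise comes from a unit's name. Nothing in the article says that the Bari inpatients received rehabilitation, how much, or that patients at the other centre received none. The common 30-day window also limits any gap in timing. This stands, and the point can be put only as plausible.

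A reader might go further and infer that the Bari controls received an active treatment, so that the comparison is biased. The documents do not support this. Any such care would come before randomisation and reach both arms, and allocation is 1:1 from centre-specific lists. Care after discharge is described in the same words at both centres. The pooled difference is a valid average over two settings.

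A reader might also infer that the pooled effect is diluted. If the effect in Bari were half as large, the pooled difference would be 0.70(1 − p) + 0.35p, that is about 0.60, 0.53 or 0.46 for a Bari share p of 30%, 50% or 70%. Power would be about 86%, 76% or 64% instead of 94%. The arithmetic is right, but both the share and the ratio are invented, and nothing in the article points to a smaller effect there. Baseline frailty is lower than planned (30.6% against 40%; EFT 1.69 and 1.89 against 2.25), which fits prior rehabilitation but equally fits the lowered age limit and the pattern of refusals.

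Finally, the authors gave sample size as their reason for planning no subgroup analyses, and by-centre tables are often left to a fuller document. The first part rightly rules out a confirmatory interaction test. The second does not remove the point, because the article itself names the adjustment set and uses one comparator label for two recruiting settings.

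**Conclusion.** The point holds as a matter of interpretation and precision, not of bias. The documents establish four things: the recruiting units differ in kind, baseline falls at the end of the stay, centre stratifies the randomisation, and the stated adjustment set is sex and SPPB. That the second centre's patients had inpatient rehabilitation before baseline is a reasonable reading but is not stated. It is not shown that the trial mixes two incompatible questions or that its effect is diluted.

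The gain in precision from including centre cannot be sized, because no outcome or baseline data are given by centre. The limits of what centre-level results can show are clear: half-widths of about 0.46 to 0.71 EFT points for a centre share of 70% down to 30%, and roughly 14% power to detect a 0.35-point difference in effect at 50:50. These figures assume 161 patients analysed and the planned SD of 1.25.

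**What to change.** - Include centre as a covariate in the models for EFT, SPPB and frailty prevalence, beside sex and SPPB, because it is the randomisation stratum and regardless of any imbalance.
- Report the EFT and SPPB differences with 95% CIs for each centre beside the pooled value, labelled descriptive. Do not rely on an interaction test, and do not read a non-significant one as evidence that the centres agree.
- Show patient numbers and baseline EFT and SPPB by centre.
- State the comparator in the conclusion as GP referral after discharge from a cardiovascular department or from a cardiac rehabilitation unit.

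The cost is one model term, one table and a few sentences. No new data are needed, since the centre strata already exist. The drawback is that the per-centre intervals will be wide and could be over-read, so the descriptive label matters.
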